### Follow-Up Procedures

Participants are followed for 14 days. They are instructed to wear the CGM and heart rate monitor. The heart rate monitor is to be always worn, including during sleep, and only removed for recharging. Participants are also asked to check their capillary glucose on days 2 through 6 before breakfast and dinner.

Participants log their full dietary intake using the study app or logbook over the 14-day study period, including all standardized test meals and free-living foods (including snacks), beverages (including water), and medications. Participants also log all exercise.

Participants are required to consume protocol-specified meals and to perform light activity, as described in Table 1. The standardized meals consist of vegetarian breakfast foods which participants are to prepare in their homes.

The meals vary in their proportion of carbohydrate, fiber, protein, and fat (refer to Table 2).

**Table 1 table1:** Meal schedule during the at-home study period.

Day and timing			Meal type
**1**			
	Breakfast	Fasting	
	Lunch	As desired	
	Dinner	As desired	
**2**			
	Breakfast	Perceived healthy meal	
	Lunch	Post meal exercise	
	Dinner	Typical mixed protein with dinner	
**3**			
	Breakfast	Fiber supplement with standardized test meal	
	Lunch	Premeal exercise	
	Dinner	Alternative mixed protein with dinner	
**4**			
	Breakfast	Fiber supplement before standardized test meal	
	Lunch	As desired	
	Dinner	As desired	
**5**			
	Breakfast	Protein supplement with standardized test meal	
	Lunch	As desired	
	Dinner	Alternative mixed protein with dinner	
**6**			
	Breakfast	Protein supplement before standardized test meal	
	Lunch	Added fiber with lunch	
	Dinner	Alternative mixed protein with added protein	
**7**			
	Breakfast	Regular breakfast	
	Lunch	Added fruit	
	Dinner	Cooled carbohydrate	
**8**			
	Breakfast	Regular breakfast with added protein	
	Lunch	Added fruit with protein	
	Dinner	Regular carbohydrate	
**9**			
	Breakfast	Protein followed by carbohydrate	
	Lunch	Water 30 minutes before lunch	
	Dinner	As desired	
**10**			
	Breakfast	Standardized test meal	
	Lunch	As desired including dessert	
	Dinner	Protein followed by carbohydrates and vegetables	
**11**			
	Breakfast	Standardized test meal with postmeal exercise	
	Lunch	As desired including desert and cinnamon	
	Dinner	Vegetables followed by protein then carbohydrates	
**12**			
	Breakfast	Standardized test meal with postmeal exercise	
	Lunch	As desired	
	Dinner	As desired finishing eating by 8 PM	
**13**			
	Breakfast	Water before late breakfast + postmeal exercise	
	Lunch	Low glycemic index lunch	
	Dinner	Low glycemic index dinner + finish dinner by 8 PM + exercise after meal	
**14**			
	Breakfast	Water before late breakfast + exercise after meal	
	Lunch	Low glycemic index lunch + exercise after meal	
	Dinner	Low glycemic index dinner + finish dinner by 8 PM + exercise after meal	

**Table 2 table2:** Nutritional composition of standardized test meals.

Meal characteristics	Meal type		
	Carbohydrate	Added fiber	Added protein
Example meal	2 aloo parathas with curd	2 aloo parathas with curd + fiber supplement	2 aloo parathas with curd + protein supplement
Energy (kcal)	474.4	506.4	594.4
Carbohydrate (g)	61.5	64.1	62.9
Fat (g)	12.5	12.5	14.6
Protein (g)	7.7	7.8	31.9
Fiber (g)	8.3	21.9	8.3
Carbohydrate (% energy)	51.9	50.6	42.3
Fat (% energy)	23.8	22.3	22.1
Protein (% energy)	6.46	6.05	21.4

Participants are instructed to fast for a minimum of 8 hours before and 3 hours after consuming the standardized breakfast meal; during these fasting periods, limit exercise and drink only still (not sparkling) water, tea, or coffee in moderation; and eat the meal, in its entirety, within 20 minutes. After completing the postmeal fasting period on standardized test meal days, participants may consume other foods as they normally would unless there are other meal modifications specified by the protocol later the same day.

On other days, participants are asked to consume normal foods with protocol-specified constraints. For example, on different days, participants vary the types of mixed protein (eg, different types of lentils with or without added protein), ordering with the type of foods consumed (eg, protein before carbohydrate vs protein with carbohydrate), consume water before their meal, go for a walk after eating, or eat what they perceive to be a healthy meal. Where applicable, participants are given several options as to which of their usual foods are acceptable for each protocol specified food modification.

During the follow-up period, participants are contacted by phone and text messages to ensure protocol compliance. For participants using the study-specific smartphone apps, a web dashboard is used to monitor the completeness of dietary logging and CGM scanning, with outreach to participants initiated when missing data is detected. Participants using paper logs and a CGM reader, and therefore for whom no dashboard information is available, are contacted daily to ask about protocol compliance. Ad hoc midstudy visits are used to further ensure accurate data collection. If the outreach identifies a problem with a CGM (ie, it was damaged, fell off, or malfunctioned), study staff provide a replacement within 24 hours during which time participants are asked to pause their meal protocol and restart once their CGM has been reapplied and recalibrated. If a test meal was not consumed as intended, participants are provided with the option to repeat the meal.

On day 15, participants are asked to remove their CGM. If need be, study staff help record or correct missing or inaccurate food, activity, and medication data.

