## Methods

This prospective cohort study seeks to evaluate the relationship between PPGR and self-management activities including diet, exercise, and other daily routines, for individuals with T2D in India (Figure 1).

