### Statistical Analysis Plan

The study’s primary outcome is PPGR. Following the Wolever and Jenkins method [31], as adapted by Zeevi et al [18], Mendes-Soares et al [20], and Berry et al [32], logged meal times and continuous glucose measurements will be used to calculate the incremental area under the curve. Before conducting analyses, meals logged less than 30 minutes apart will be merged and meals logged within 90 minutes of other meals will be removed. Meals that are very small (<15 g and <70 calories), very large (>1 kg), with implausibly low PPGR values (ie, a PPGR < 5 mg/dL·h after consuming ≥ 40 g of carbohydrates), that are incompletely logged, and which are consumed in the first and last 12 hours of the CGM connection will also be removed. To reduce noise, the median of all glucose values from the 30-minute period before the meal will be taken as the initial glucose level, above which the incremental area will be calculated. Meals that had incomplete glucose measurements in the time window of 30 minutes before and 2 hours after the logged mealtime will be filtered out.

Descriptive statistics will be used to plot the range of PPGRs responses to standardized test meals as well as the correlation between PPGR and the nutritional composition of the logged meals (ie, carbohydrates, fat, and protein).

A machine learning predictor will be developed based on stochastic gradient boosting regression (XGBoost, version 2.2.1; The XG Boost Contributors) [33] using the XGBRegressor class. PPGR will be predicted as the sum of predictions from thousands of decision trees. Trees will be inferred sequentially, with each trained on the residual of all previous trees. The features incorporated in each tree are selected by an inference procedure from features representing meal content (ie, calorie, protein, carbohydrate, and fiber content), meal timing, baseline demographics (ie, age, sex, predominant diet, health conditions, family history, and current medications), baseline survey results (ie, WHO STEPS, WHO-5, Diabetes Distress School, Wilson Adherence Scale, and Pittsburgh Sleep Quality), baseline biometric values (ie, blood pressure, heart rate, weight, height, and body measurements at the upper arm, thigh, calf, waist, and hips), baseline laboratory values (complete blood count, HbA_1c_, blood electrolytes, creatinine, cholesterol, and urinalysis), as well as CGM, heart rate, and activity data.

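### Six kinds of imposed meal condition, on 14 of the 41 scheduled meals, are not in the stated predictor list and should be coded as meal-level features

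*Protocol article*

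**What the plan says.** The Methods section opens with the aim to "evaluate the relationship between PPGR and self-management activities including diet, exercise, and other daily routines". Table 1, under Follow-Up Procedures, then prescribes a condition for many individual meals. Some act through what is eaten or when (added fiber, added protein, an early dinner) or through exercise. Others do not, such as the day 11 lunch, "As desired including desert and cinnamon", the eating-order meals on days 9 to 11, and the day 13 breakfast, "Water before late breakfast + postmeal exercise". The dinners on days 13 and 14 carry the same entry, "Low glycemic index dinner + finish dinner by 8 PM + exercise after meal".

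Away from the standardized breakfasts the base food is the participant's own: "On other days, participants are asked to consume normal foods with protocol-specified constraints". The same section adds: "Where applicable, participants are given several options as to which of their usual foods are acceptable for each protocol specified food modification". No stated rule requires the same food or portion on two days that form a natural pair.

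The Statistical Analysis Plan section says the trees draw on "features representing meal content (ie, calorie, protein, carbohydrate, and fiber content), meal timing", followed by baseline demographics, surveys, biometrics and laboratory values, and by CGM, heart rate and activity data. Meal content is given as a closed list. The assigned condition does not appear.

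**The concern.** A boosted-tree model can use only the features it is given. If a meal is eaten vegetables first, or after a water preload, and nothing in its data row says so, the model sees an ordinary meal with those nutrients at that hour. Any effect of the condition then goes into the residual or is attributed to a nutrient that happens to travel with it. Participants carry the burden of a detailed schedule, and the sponsor knows the condition of each scheduled meal, yet the stated model does not use it. What is at stake is the diet and daily-routine part of the aim and the credibility of nutrient attributions behind personalized advice. The definition of PPGR is not affected.

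**Working it through.** **1. The plan's own meal count.** Sample Size Considerations gives 42,000 meals: 1000 participants × 14 days × 3 meals = 42,000, which reproduces. Per participant that is 42 slots. Table 1 marks day 1 breakfast as fasting; read as no meal, 41 remain.

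**2. Meals with a condition the listed features do not represent** (B, L, D = breakfast, lunch, dinner). Meal timing is read as the time of the meal.
- Food order: 9B, 10D, 11D (3)
- Supplement before the standardized meal: 4B, 6B (2)
- Cooled carbohydrate: 7D (1)
- Cinnamon: 11L (1)
- Water preload: 9L, 13B, 14B (3)
- Low glycemic index: 13L, 13D, 14L, 14D (4)

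Total 3 + 2 + 1 + 1 + 3 + 4 = 14. As a share, 14/41 = 34% (14/42 = 33% if day 1 breakfast is counted). Without the two standardized breakfasts, 12 are free-living: 12/41 = 29%. Exercise, clock time, added fiber and added protein are not counted, because activity, timing and nutrient features can carry them.

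**3. Which components can be separated.** Table 1 was coded as component indicators in an additive model with an intercept per slot, leaving out day 1 breakfast. The coding is the reviewer's.

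| Slot | Meals | Columns | Rank | Not separable |
|---|---|---|---|---|
| Breakfast | 13 | 10 | 9 | water and late eating (only days 13 and 14, always together) |
| Lunch | 14 | 10 | 10 | none |
| Dinner | 14 | 11 | 10 | low glycemic index and post-meal exercise (only days 13 and 14, always together) |
| All slots pooled | 41 | 24 | 24 | none, if a component acts alike in every slot |

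Lunch separates because day 13 has low glycemic index alone and day 14 adds exercise. At dinner the 8 PM finish separates through day 12, where it occurs alone.

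**4. Free choice of base meal on paired days.** The pairs are days 7/8 (breakfast without and with protein, fruit without and with protein, cooled versus regular carbohydrate) and days 10/11 (dessert without and with cinnamon). Assume base-meal carbohydrate varies within a person with a CV of 20-30% and PPGR is proportional to it; neither figure is in the article. The SD of one within-pair difference is CV × √2, or 0.20 × 1.414 = 28% to 0.30 × 1.414 = 42% of the mean. Averaged over 1000 participants, the SE is 28%/√1000 = 0.9% to 42%/√1000 = 1.3%. Random food choice therefore hides an effect in one person's pair but not an average effect. A systematic switch of food between the two days does not average out.

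**5. How much the omission could add to the residual.** As an illustration, assume one common effect of 10-15% of mean PPGR on all 14 meals. Its SD over meals is effect × √(p(1 − p)) with p = 14/41, and √(0.341 × 0.659) = 0.474. That gives 0.10 × 0.474 = 4.7% to 0.15 × 0.474 = 7.1% of the mean, before nutrients absorb any part of it. The likely gain is clearer attribution more than a large rise in predictive correlation.

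**The case against.** The strongest reply is that the article promises no effect estimate for any single modification. It plans a description of responses to standardized meals, correlations with nutrients, and a prediction model, and its Limitations section calls the approach deliberately pragmatic. On that view the modifications only add variation, and coding detail belongs in a full protocol or SAP that is not shown. Much of this stands. It removes any claim that the design fails, and any complaint that contrasts are undefined. It does not remove the narrower point: the article does state its feature list, the list leaves these conditions out, and the aim covers diet and daily routines.

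A reader might infer more than the documents support:
- **That the effects of the modified meals cannot be read at all.** Nutrients are logged and can be adjusted for, random base-meal noise averages to about 1% over 1000 people, and the pooled coding has full rank if components act alike across slots.
- **That days 13 and 14 never separate their components.** Lunch does. Post-meal exercise at day 2 lunch, water at day 9 lunch and the 8 PM finish at day 12 dinner also occur alone.
- **That no imposed condition reaches the model.** Exercise, timing, fiber and protein do, through listed features. Low glycemic index may be partly reflected in carbohydrate and fiber content.
- **That the schedule should be changed.** Dropping exercise from one of the day 13-14 breakfasts would still leave water tied to late eating, would give up a within-person repeat, and would split a cohort enrolling since May 2022 between two schedules.

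**Conclusion.** The point holds as a specific, nearly free improvement to the stated model. Six kinds of imposed condition, on 14 of 41 scheduled meals (34%; 12 of them free-living), have no counterpart among the listed predictors. Their effects would fall into the residual or be credited to nutrients. Two pairs of components, water with late eating at breakfast and low glycemic index with exercise at dinner, cannot be separated within their slot, and indicators will not change that. Comparisons between paired free-living days also carry any systematic change of food.

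The conclusion rests on reading the predictor list as complete and meal timing as the time of the meal. If the full analysis plan already codes the conditions, only the article's list needs correcting. The base-meal CV and the effect size are assumptions, and the count of 14 does not depend on them.

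**What to change.** - Add to the feature set, for all participants including those already enrolled, meal-level indicators for food order (distinguishing the sequences used), supplement before versus with the meal, cooled carbohydrate, cinnamon, water preload and low glycemic index. Code them from the meal actually eaten and not from the calendar day, because Follow-Up Procedures allows the meal protocol to be paused and test meals to be repeated. Do not rely on log times for order: entries less than 30 minutes apart are merged, so courses logged separately could lose their sequence.
- Interpret the day 13-14 breakfasts and dinners only as bundles within their slot.
- Where days 7/8 or 10/11 are compared, adjust for logged nutrients and portion, and state that the same base meal was not required.

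The cost is a few extra coded variables. The meal schedule stays as it is. One limit remains: under the single schedule shown, condition is confounded with study day, and this should be stated beside any condition-specific result.

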### Statistical Analysis Plan

The study’s primary outcome is PPGR. Following the Wolever and Jenkins method [31], as adapted by Zeevi et al [18], Mendes-Soares et al [20], and Berry et al [32], logged meal times and continuous glucose measurements will be used to calculate the incremental area under the curve. Before conducting analyses, meals logged less than 30 minutes apart will be merged and meals logged within 90 minutes of other meals will be removed. Meals that are very small (<15 g and <70 calories), very large (>1 kg), with implausibly low PPGR values (ie, a PPGR < 5 mg/dL·h after consuming ≥ 40 g of carbohydrates), that are incompletely logged, and which are consumed in the first and last 12 hours of the CGM connection will also be removed. To reduce noise, the median of all glucose values from the 30-minute period before the meal will be taken as the initial glucose level, above which the incremental area will be calculated. Meals that had incomplete glucose measurements in the time window of 30 minutes before and 2 hours after the logged mealtime will be filtered out.

Descriptive statistics will be used to plot the range of PPGRs responses to standardized test meals as well as the correlation between PPGR and the nutritional composition of the logged meals (ie, carbohydrates, fat, and protein).

A machine learning predictor will be developed based on stochastic gradient boosting regression (XGBoost, version 2.2.1; The XG Boost Contributors) [33] using the XGBRegressor class. PPGR will be predicted as the sum of predictions from thousands of decision trees. Trees will be inferred sequentially, with each trained on the residual of all previous trees. The features incorporated in each tree are selected by an inference procedure from features representing meal content (ie, calorie, protein, carbohydrate, and fiber content), meal timing, baseline demographics (ie, age, sex, predominant diet, health conditions, family history, and current medications), baseline survey results (ie, WHO STEPS, WHO-5, Diabetes Distress School, Wilson Adherence Scale, and Pittsburgh Sleep Quality), baseline biometric values (ie, blood pressure, heart rate, weight, height, and body measurements at the upper arm, thigh, calf, waist, and hips), baseline laboratory values (complete blood count, HbA_1c_, blood electrolytes, creatinine, cholesterol, and urinalysis), as well as CGM, heart rate, and activity data.

Performance will be assessed by holding out 30% of the sample and using 5-fold cross-validation in which cross-validation participants are divided into 5 groups, the model will be trained on the other 4 parts. Random datasets of the same size as the original will be sampled with replacement from the original dataset, and the entire training and validation process will be repeated. The performance will be measured by the ability to accurately predict meals reported by the held-out participants. Prediction results will be aggregated, and Pearson product moment correlation with the measured PPGRs will be reported. The SE for the calculated performance will be assessed using at least a thousand iterations of bootstrapping until the errors stabilize. Model discrimination will be assessed using a binary cut-point for PPGR, set at the 50th percentile of all observed PPGR values, plotting a receiver operating characteristic curve (ROC) and then calculating the area under the ROC.

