**Methods:**

Adults with T2D and a hemoglobin A_1c_ of ≥7 are being enrolled from 14 sites around India. Participants wear a continuous glucose monitor, eat a series of standardized meals, and record all free-living foods, activities, and medication use for a 14-day period. The study’s primary outcome is PPGR, calculated as the incremental area under the curve 2 hours after each logged meal.

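### Free-living meals eaten soon after the 90-minute cut-off take their baseline from the earlier meal's glucose excursion, so their PPGR is biased downward by an amount set by the gap and relative meal size

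*Protocol article*

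**What the plan says.** The primary outcome is PPGR, "calculated as the incremental area under the curve 2 hours after each logged meal" (Abstract, Methods). The Statistical Analysis Plan section fixes how it is derived:

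- Spacing: "meals logged within 90 minutes of other meals will be removed", after a first step in which "meals logged less than 30 minutes apart will be merged". A meal more than 90 minutes from its neighbours is kept.
- Baseline: "the median of all glucose values from the 30-minute period before the meal will be taken as the initial glucose level". Only the area lying over this level counts towards PPGR.
- Low-value filter: a meal is removed as implausible if it has "a PPGR < 5 mg/dL·h after consuming ≥ 40 g of carbohydrates".
- Small-meal filter: only entries under both 15 g and 70 calories are removed, so most snacks stay.

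Follow-Up Procedures has participants log all foods, snacks included. For the standardized breakfast alone, they must "fast for a minimum of 8 hours before and 3 hours after consuming the standardized breakfast meal". No comparable condition applies before free-living lunches, dinners or snacks. These meals enter the PPGR-nutrient correlations and the XGBoost predictor.

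**The concern.** PPGR is used as the response to the logged meal. If food was eaten about 90 minutes to 3 hours earlier, the 30-minute baseline window can fall while glucose is still raised by that food. Two things then push the later meal's PPGR down. The reference level is too high, and the earlier excursion usually falls during the later meal's 2-hour window, which offsets part of its rise.

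The shortfall depends on the earlier food and the gap, not on the meal being scored. Snacks and the meals of frequent eaters would look more benign than they are. That would distort the correlations between PPGR and nutrient content, the outcome on which the predictor is trained and tested, and the 50th-percentile PPGR cut-point used for the ROC curve. Extending the spacing rule to match the 2-hour outcome window would not cure it, because the bias is still large at 120 minutes.

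**Working it through.** **The plan's own figure.** There is none to reproduce. The article gives no postprandial curve, meal spacing or snack frequency.

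**Inputs from the article.** Baseline: median of the prior 30 minutes. Readings: every 5 minutes (Sample Size Considerations). Outcome: area above baseline over 0-2 hours, with area below baseline counted as zero. Meals more than 90 minutes apart are kept.

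**Assumptions, not in the article.** A flat underlying level. Each meal adds a rise A·(x·e^(1−x))^k, where x = minutes since the meal ÷ time to peak. Responses add. The comparator is the same second meal eaten with no earlier meal. Percentages depend on the ratio of the two rises, not on their absolute size.

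**One case by hand.** Peak at 60 minutes, k = 3, both rises 80 mg/dL, gap 120 minutes.

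1. Residual glucose from meal 1 at the six baseline readings (90 to 115 minutes after meal 1): 60.2, 55.2, 50.1, 45.2, 40.5, 36.0. The median is (50.1 + 45.2)/2 ≈ 47.7 mg/dL above the true resting level.
2. Meal 2 eaten alone: PPGR 101.0 mg/dL·h.
3. Area still contributed by meal 1 during meal 2's 2 hours: 17.7 mg/dL·h.
4. Signed area = 101.0 + 17.7 − 2 × 47.7 ≈ 23.4. Counting only area above baseline gives 31.2.
5. Loss = 1 − 31.2/101.0 = 69%.
6. With meal 2 a quarter of the size (alone 25.3), signed area = 25.3 + 17.7 − 95.3 = −52.3. Glucose never exceeds the baseline, so the scored PPGR is 0.

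**Range over 12 curves** (peak 45, 60, 75 or 90 minutes; k = 1, 2 or 3). Entries are percent understatement, lowest to highest.

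| Gap (min) | Equal meals | Second half the first | Second a quarter of the first | Second 3 times the first | Second 4 times the first |
|---|---|---|---|---|---|
| 95 | 21-88 | 42-100 | 72-100 | 7-35 | 5-26 |
| 120 | 33-81 | 65-100 | 97-100 | 11-29 | 8-22 |
| 150 | 13-72 | 25-100 | 46-100 | 4-25 | 3-19 |
| 180 | 3-53 | 6-97 | 13-100 | 1-19 | 1-14 |
| 240 | 0-30 | 0-59 | 1-100 | 0-10 | 0-7 |

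On the narrower set of six curves (peak 60-90 minutes, k = 2 or 3), equal meals lose 41-88% at 95 minutes, 60-81% at 120, 37-72% at 150, 16-53% at 180 and 2-29% at 240.

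Over the 12 curves and gaps of 90 to 180 minutes, equal meals lose a third or more in 81% of combinations (7 of 12 curves at 180 minutes). A quarter-size snack scores essentially zero in 75%.

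**Interaction with the filters.** The low-value rule acts only at 40 g of carbohydrate or more. A smaller snack scoring zero stays in as a zero. A larger affected meal scoring below 5 mg/dL·h is deleted, so at that end the carry-over becomes selection on a distorted outcome.

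**The case against.** The fair case against is that the plan follows cited methods, describes itself as pragmatic, and defines PPGR relative to whatever the pre-meal level is. On that view a meal-eaten-alone response is not its target for free-living meals. Meal timing and CGM data are already listed as model features, and a condensed article may leave sensitivity analyses to a fuller plan.

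Part of this stands. The features may let the model learn some of the carry-over. They do not correct the outcome itself, the nutrient correlations or the ROC cut-point. The Discussion also names prediction with little or no CGM data as a key goal, and in that setting the CGM features would be largely absent. The point does not rest on an omission: the spacing and baseline rules are written down, and the bias follows from them.

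Four stronger readings are tempting and are not supported:

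- That every such meal is understated by a third or more. This fails for a main meal after a small snack (apart from the slowest curves at about 95 minutes with a one-third-size snack) and at 3 hours when glucose returns fast.
- That glucose is always still falling in the baseline window. With a 90-minute peak and a 90-minute gap, the baseline sits near the peak.
- That the description of interindividual variability is compromised. The planned range plots use standardized test meals, and the 8-hour fast before them protects their baseline.
- That the protocol already sets a 3-hour washout before meals. Its 3 hours follow the test meal; the period before it is 8 hours.

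**Conclusion.** The concern holds as a directional bias of uncertain size in the free-living PPGRs. In every case tried, the written rule lowered or left unchanged the second meal's PPGR. Under the assumed additive curves the loss is roughly 15-90% for equal meals 95-180 minutes apart, down to 3% at 180 minutes on the fastest-returning curve. It is about 1-30% for a main meal after a small snack, and can be total for a small snack after a large meal.

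The size rests on the assumed curve shapes, additivity and a flat underlying level, none of which the article supplies. How many free-living meals fall in this band is unknown and could be small; any percentage drawn from the meal schedule would need invented snack times. The test-meal description is not affected. This is a cheap improvement to the plan, not a reason to discard the 90-minute rule.

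**What to change.** Keep the 90-minute set as the main set if preferred. Prespecify a repeat of the PPGR-nutrient correlations, and of predictor training and testing, restricted to meals with no energy-containing entry in the previous 3 hours, plus a 4-hour version. State that 3 hours is a chosen threshold and not the protocol's own pre-meal fast. Report how many meals each restriction removes, which would also show how common the problem is.

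In all sets, enter minutes since the last energy-containing entry and that entry's carbohydrate as explicit features. Add the pre-meal glucose slope where CGM features are used.

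The cost is one filter and three derived variables from data already collected. The downside is that the restricted sets are smaller and represent frequent eaters less well. Some bias also remains: at a gap of exactly 3 hours, 3-53% for equal meals; at 4 hours, 0-30%, and more for small snacks on slow curves. The comparison across sets therefore shows whether conclusions depend on carry-over; it does not remove it.
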